### Conceptual framework

Prior research and theory indicate that motivation and agency are mechanisms underlying smoking cessation treatment enrollment, and motivation, agency, and stress/negative affect are key mechanisms of quitting smoking [58–66]. ST and AT were designed to address these mechanisms. We hypothesize similar mechanisms between the 2 groups (ST vs. AT); however, we do not expect equal magnitudes of effect. A secondary aim is to evaluate the magnitude of the mediated effects between ST and AT. For example, ST participants might report more motivation to quit smoking, but AT participants may report higher self-efficacy. See Fig. 2.

**Fig. 2 Fig2:**
[figure not shown]
Hypothesized mechanisms underlying Standard Treatment (ST) and Automated-Treatment (AT)

#### Motivation

Motivation refers to one’s willingness or desire to change a behavior [67], and it plays a critical role in decisions related to behavior change and in the likelihood of achieving and maintaining change (see [58, 59]). Motivation is characterized by frequent fluctuations. In the context of smoking, over one-third (41%) of US smokers report daily changes in their motivation to quit smoking [68], and most quit attempts are unplanned [69, 70]. Shortly after quitting, motivation may weaken, and ambivalence may increase as individuals experience withdrawal symptoms and are exposed to high-risk situations and stressors [61]. Given its influences on the initiation of a quit attempt, cessation success, and the maintenance of abstinence, motivation should be targeted in treatment [38].

#### Agency (sense of control, self-efficacy)

Human agency**—**the ability to purposefully affect one’s behavior or life situation—is influenced by personal resources and situational factors [71, 72]. Concepts encompassed under agency include sense of control and self-efficacy [72]. Sense of control is the learned expectation that outcomes are not caused by chance, other people, or forces outside of one’s control, but rather, they depend on one’s personal choices and previous actions [41, 73]. Self-efficacy refers to an individual’s belief in their capacity to change a behavior [74], and it is dependent on context and behavior [73, 75]. Self-efficacy is among the strongest and most-studied predictors of smoking cessation treatment outcomes [63, 64, 76, 77].

#### Stress/negative affect

Stress-coping [78] and self-medication [79] models of substance use purport that people use substances to regulate mood and manage stress. Smokers often report smoking more when experiencing a negative mood (e.g., anxiety, sadness, anger, stress) and expect that smoking will help with managing these symptoms [66, 80, 81]. Additionally, there appears to be a dose-response relationship between stress/negative affect and smoking, such that greater distress is associated with higher nicotine dependence and heavier (vs. intermittent) smoking [82]. Regarding quitting, the magnitude and trajectory of stress/negative affect over time predict cessation [83, 84], as do individual differences in affective vulnerability [85, 86]. Research suggests that stress, negative affect, and psychological distress are associated with poorer smoking cessation treatment outcomes [77, 87–90], and most smokers report experiencing elevated negative affect after quitting, regardless of whether they use NRT [91].

#### Reciprocal relations among mechanisms

Reciprocal relations have been established among our key hypothesized mechanisms [61, 77, 92–94]. We hypothesize that ST and AT will reduce stress/negative affect via the following mechanisms: 1) reducing ambivalence and increasing motivation; 2) using coping skills training and problem solving to increase self-efficacy; and 3) using a holistic treatment approach to address other life concerns and stressors. We also expect that reductions in stress/negative affect will increase motivation and agency.

### Treatment groups

We created ST and AT to expand the reach of our existing evidence-based AAC model [7, 8] into the community. Both approaches involve the systematic assessment of smoking status (Ask) among individuals seeking food bank assistance, delivery of brief advice to quit to smokers (Advise), and an immediate offer of enrollment in treatment (Connect). Brief advice to quit will be delivered to all participants using a pre-recorded video clip. This automated approach to delivering brief advice to quit will standardize delivery across conditions, thus enhancing the future scalability and dissemination potential of AT.

We designed ST to mirror a clinic-based AAC model, as it consists of the standard Quitline-delivered services offered to uninsured smokers in Florida. AT will function as a fully-automated program capable of delivering smartphone-based treatment content that includes interactive messaging, images, and audiovisual clips. The AT intervention delivery period will span 26 weeks, with 12 weeks of proactive content and 26 weeks of on-demand access. All participants will receive a 10-week supply of combination NRT (nicotine patches and lozenges). Nicotine patches provide a low, constant dose of nicotine, which reduces nicotine withdrawal symptoms (e.g., physical symptoms, negative affect) after quitting, while lozenges provide a fast-acting dose of nicotine that helps to manage cravings. When combined with behavioral treatment, NRT effectively doubles the odds of quitting [95].

#### Standard treatment (ST)

After the baseline assessment and brief advice to quit video, we will provide participants with 10 weeks of nicotine patches and lozenges. We will connect ST participants with Florida Quitline services, where they will receive smoking cessation treatment delivered by the Quitline. Participants will complete weekly 4-item smartphone assessments for 26 weeks. Weekly assessments will consist of questions on smoking status, motivation, self-efficacy (to measure agency), and perceived stress (to measure stress/negative affect).

#### Automated treatment (AT)

Following the baseline assessment and brief advice to quit video, AT participants will be given a 10-week supply of nicotine patches and lozenges. AT will consist of: 1) 12 proactive treatment videos (delivered weekly) tailored on smoking status, motivation, agency, and/or negative affect/stress; 2) 26 weeks of on-demand access to treatment content; and 3) 26 weeks of text content.

AT participants will complete weekly 4-item assessments of smoking status, self-efficacy, motivation, and stress for 26 weeks. An algorithm will use participants’ responses to deliver brief (2–6 min) videos from a library of tailored content. See Table 2 for a list of weekly topics. The app will deliver the most suitable video each week, expressly tailored for each participant. During the first 12 weeks, weekly videos will be automatically launched after the completion of assessments. Referrals to other relevant treatment resources will be available through the app. These will include phone numbers for substance abuse treatment centers, psychiatric services, and social services.

**Table 2 Tab2:** Automated Treatment session topic by study week

Week	Topic
Week 1	Preparing to Quit
Week 2	Quit Day
Week 3	What to Do if You Have a Cigarette
Week 4	Nicotine Patches and Lozenges
Week 5	Smoking, Stress, and Mood
Week 6	Health Benefits of Quitting
Week 7	Smoking and Your Weight
Week 8	Staying on Track
Week 9	Financial Benefits of Being a Nonsmoker
Week 10	Taking Care of Yourself
Week 11	Social Benefits of Being a Nonsmoker
Week 12	Life without Cigarettes

The AT app was designed to function autonomously and require minimal human involvement, while being suitable for implementation in various environments. The AT approach is expected to outperform but share common mechanisms of action with the current standard of care (i.e., quitline counseling). The app consists of both a staff-facing dashboard and a mobile application. Videos were created with the Adobe After Effects animation software package.

Based on our prior work and the extant literature supporting the efficacy of text message-based smoking cessation interventions, AT participants will also receive smartphone-delivered text content [24, 84]. This content will be delivered using notifications generated by the app. Participants will receive one message per day for the first 12 weeks and one per week in weeks 13–26. Notifications will start just before the scheduled quit date and will continue throughout the 26-week treatment period. Content was designed to target the hypothesized mechanisms, promote NRT adherence, and encourage participants to access on-demand content within the app. The text content will refer to participants by their first name to personalize treatment.

### Measures and assessment strategy

Several factors guided our assessment strategy. First, we attempted to include psychometrically-sound measures with established reliability and validity, and measures without established reliability and validity were required to have face validity. Second, measures had to either: 1) describe the sample; 2) predict smoking behavior; or 3) represent our hypothesized mechanisms. Notably, all the measures are based on theory, models of health behavior or nicotine dependence, and/or existing data. Third, to ensure a representative sample of smokers, we will recruit both English- and Spanish-speaking participants. The Florida Quitline is equipped to provide treatment in English and Spanish, and the mobile app (AT) will be available in both languages. Most of the measures were previously translated and validated in Spanish, and a certified translator will be used for measures that have not yet been translated. Finally, to reduce participant burden, participants will have the option of completing assessments in person, over the phone, or online. REDCap will be used to administer all assessments. REDCap is a secure, web-based app designed to support data collection. It will support the secure capture of data for cleaning, storage, and analysis. Moffitt Cancer Center is a member of the REDCap Consortium.

#### Primary outcomes

Our primary outcome is self-reported 7-day smoking abstinence at the 12-month follow-up. We will examine other definitions of abstinence (e.g., biochemically-verified abstinence using salivary cotinine, self-reported 24-h, 30-day, and continuous abstinence) as secondary outcomes. Participants reporting smoking abstinence will be mailed a saliva cotinine kit with instructions for providing the cotinine sample. Research staff will be available by phone and email to answer questions about the cotinine collection process. Participants will be asked to return cotinine samples using a prepaid envelope.

Regardless of treatment group assignment, participants will complete brief 4-item weekly smartphone-delivered assessments throughout the 26-week treatment period. AT participants will receive assessments via the app, and ST participants will receive assessments through a REDCap link via email or text (based on their preference). Assessments will be identical for ST and AT participants, but responses will be used to select appropriate treatment content for AT participants, as previously described.

#### Assessment of treatment engagement-related variables in AT

In addition to evaluating the efficacy of AT, we will track and examine the frequency and duration of AT participants’ app interactions. Interactions will be date and time stamped, and we will note the specific app features used by participants. This will allow us to examine the frequency and duration of participants’ utilization of various app components and the conditions under which they engage with components of the app. This information will guide future iterations of the app.

### Data analysis plan

Prior to inferential procedures, extensive descriptive analyses will be conducted to review variable distributions. In addition, descriptive statistics will characterize the sample and summarize the frequency and duration of participants’ interactions with the app. Exploratory analyses will examine how the utilization of various AT treatment components is associated with participants’ perceptions of the app and with cessation outcomes.

#### Primary aim

Our overarching aim is to evaluate the efficacy of AT on facilitating smoking abstinence. The primary outcome is self-reported 7-day point prevalence abstinence at the 12-month follow-up. We hypothesize that smoking abstinence rates will be higher in the AT (vs. ST) group. Using intention-to-treat methodology, we will code participants who do not complete follow-up as smoking. We will test this hypothesis using log-binomial regression, with intervention group as the primary predictor. We will control for relevant covariates (e.g., baseline nicotine dependence) and examine if treatment effects differ by sex assigned at birth.

Comparable analyses will evaluate the interventions’ effects on other definitions of smoking abstinence, including biochemically-verified abstinence using salivary cotinine and self-reported 24-h, 30-day, and continuous abstinence. We will also use smoking status at 3- and 6-months to evaluate the efficacy of AT. Generalized linear mixed models (GLMMs) with a log link function and the appropriate random-effect covariance structure will be used to analyze these data. Intervention, time, and their interaction will be included and tested in the model.

#### Secondary aim 1

We will evaluate the magnitude of the mediated effects via common mechanisms (i.e., motivation, agency, stress/negative affect) on smoking abstinence. Although we hypothesize common mechanisms of AT and ST, it will be important to pinpoint the relative strengths and weaknesses of the mechanisms in facilitating abstinence. These hypotheses can be tested using mediation analyses with intervention group (ST vs. AT) as the independent variable, abstinence at 12 months as the outcome variable, and the hypothesized mechanisms (motivation, agency, stress/negative affect) as potential mediators. To test these hypotheses, we will fit single and multiple mediator models, using the approaches of MacKinnon and colleagues [96] and Preacher and Hayes [97–99].

#### Secondary aim 2

We will conduct economic evaluations from a societal and a health system perspective to determine the cost and cost-effectiveness of both interventions. We will perform conventional cost-effectiveness analysis to summarize results as the incremental cost-effectiveness ratio (ICER; [100–102]). The ICER estimates additional resources needed to achieve an increase in units of effectiveness. The ICER is calculated as the difference in mean costs between a new (i.e., AT) and standard treatment (i.e., ST) divided by the difference in mean effectiveness between the treatments. The ICER is then compared with a published threshold value associated with a known cost-effective intervention. Two commonly-used measures—number of quitters and years of life saved (YOLS; [103])—will be used to compare the ICER with published cost-effectiveness studies. We will use data from the 12-month follow-up to calculate number of quitters for ST and AT. We will determine YOLS using a published algorithm that models YOLS per quitter [104]. This algorithm will incorporate recent estimates of age-specific smoking-related deaths [105]. We will also include quality-adjusted life years (QALY), which will be calculated using the EQ-5D-5L [47], a measure of health utilities.

We will use the net benefit approach to avoid the issue of zero denominators and to address uncertainty [106, 107]. This approach transforms the ICER into the net benefit, defined as NB(λ) = λ x ΔE – ΔC, where λ represents societal willingness to pay (WTP), ΔC represents incremental costs, and ΔE represents incremental effectiveness. We will report results both in terms of the conventional ICER and the cost-effectiveness acceptability curve—the latter can be used to inform decision makers of the probability that AT is more cost-effective than ST at various levels of societal WTP. This approach can be incorporated into a regression framework, which allows for covariate adjustments and the testing of interaction effects [108].

Finally, we will assess the short- and long-term economic impact of both interventions. For the short-term analysis, we will use number of quitters as the effectiveness measure and we will assess cost-effectiveness with data from the 3-, 6-, and 12-month follow-ups. For the long-term analysis, we will extrapolate the intervention effect to lifetime, using YOLS and QALY. Starting in the second year, a 3% discount rate will be applied to costs and outcomes. First, we will conduct deterministic analysis, where we will calculate point estimates of ICERs or cost differences. We will apply nonparametric bootstrapping methods to the person-level data to obtain 95% confidence intervals [109]. Next, we will conduct 1-way sensitivity analyses to elucidate the impact of alternative outcomes and measures of cost. We will then use a Bayesian approach to construct the cost-effectiveness acceptability curve and perform probabilistic sensitivity analysis [110, 111]. Bayesian analysis will be conducted with WinBUGS or STATA. Costs will be modeled as a gamma or lognormal distribution and abstinence as a binomial distribution. Finally, we will conduct regression-based cost-effectiveness analysis. Individual-level net benefit will be regressed on covariates, plus a binary variable reflecting intervention group (ST vs. AT). The model will be analyzed in 2 ways: 1) GLMM to examine cost-effectiveness over time and 2) Bayesian regression to systematically update information gathered at each time point.

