#### Power considerations

Participants who do not complete follow-up will be classified as smokers for the primary analysis. We estimated power for self-reported abstinence between treatment groups at the 12-month assessment [114]. Based on findings from our AAC implementation study [9, 10], we expect an abstinence rate of 5% in ST. With 250 participants per group, a 2-group large-sample normal approximation test of proportions with a 2-sided 0.05 significance level will have 80% power to detect an increase in abstinence of 7% in AT vs. ST.

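### The log-link mixed model for repeated abstinence does not bound person-level probabilities at 1, and can inflate the risk ratio when abstinence is strongly correlated within person

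*Protocol article*

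**What the plan says.** All of this is in the Protocol article, Data analysis plan.

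- **Primary analysis (Primary aim).** "The primary outcome is self-reported 7-day point prevalence abstinence at the 12-month follow-up", and "We will test this hypothesis using log-binomial regression, with intervention group as the primary predictor".
- **Repeated analysis (Primary aim).** "We will also use smoking status at 3- and 6-months to evaluate the efficacy of AT". The model follows: "Generalized linear mixed models (GLMMs) with a log link function and the appropriate random-effect covariance structure will be used to analyze these data". Its fixed part is also given: "Intervention, time, and their interaction will be included and tested in the model". I read this as one model over the 3-, 6- and 12-month visits.
- **Planned rates (Power considerations).** "we expect an abstinence rate of 5% in ST", with "80% power to detect an increase in abstinence of 7% in AT vs. ST".

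The link and the model class are therefore fixed. The response family and the distribution of the random effects are not named. The families named for abstinence elsewhere are log-binomial, for the primary test, and binomial, in the economic model (Secondary aim 2).

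**The concern.** In a log-link mixed model, person i at visit t has probability exp(fixed part + random effect). A normal random effect has no upper limit, so neither has this probability. Binary data cannot follow such a model exactly, and the misfit grows with the spread of the random effect, that is, with the within-person correlation. Abstinence at successive visits is plausibly strongly correlated. Counting non-completers as smokers is likely to add to this, because a participant who drops out stays coded as a smoker.

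There are two usual ways to fit the model. A binomial likelihood is undefined where the probability exceeds 1, so the fit fails or relies on an undocumented cap. A Poisson likelihood converges but has the wrong variance for 0/1 data.

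At stake are the 3- and 6-month efficacy estimates and the intervention-by-time results. They could carry an overstated risk ratio, or force a change of model after the data have been seen.

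**Working it through.** **1. The plan's own figure.** Inputs from Power considerations: "With 250 participants per group, a 2-group large-sample normal approximation test of proportions with a 2-sided 0.05 significance level", ST 5%, AT 5% + 7 points = 12%. The pooled rate is 0.085.

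z = [0.07 × √250 − 1.96 × √(2 × 0.085 × 0.915)] / √(0.05 × 0.95 + 0.12 × 0.88) = 0.853, so power is 80.3%. The stated 80% reproduces. This calculation does not involve the mixed model.

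**2. How much of the model lies above 1.** Let p be the abstinence rate and q the chance that an abstainer is abstinent again at the next visit. The document gives no q; 40-80% is assumed. For a normal random intercept with SD s:

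- exp(s²) = q/p
- intercept m = ln p − s²/2
- share of people above 1 = P(Z > −m/s)
- share of modelled abstinence carried by those people = P(Z > (−m − s²)/s)

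Example, p = 0.12 and q = 0.60: s² = ln 5 = 1.609, s = 1.269, m = −2.120 − 0.805 = −2.925. People above 1: P(Z > 2.306) = 1.06%. Share of abstinence: P(Z > 1.037) = 15%.

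| p | q | s | people above 1 | share of modelled abstinence |
|---|---|---|---|---|
| 5% | 40% | 1.44 | 0.26% | 9% |
| 5% | 60% | 1.58 | 0.36% | 13% |
| 5% | 80% | 1.67 | 0.42% | 17% |
| 12% | 40% | 1.10 | 0.66% | 8% |
| 12% | 60% | 1.27 | 1.06% | 15% |
| 12% | 80% | 1.38 | 1.29% | 20% |

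Few people exceed 1, but they carry 8-20% of the modelled abstinence. The implied within-person correlation is p(exp(s²) − 1)/(1 − p). At p = 12% and s = 1.5 it is 0.12 × 8.49/0.88 = 1.16, which is impossible.

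**3. Effect on the risk ratio, Poisson fit.** Trials with 250 per arm and three visits were simulated from correlated latent normal variables. ST rates were 8/6/5% and AT rates 18/14/12% at 3/6/12 months. Only the 12-month rates come from the protocol; the others, and the latent correlations, are assumed. True risk ratios are 2.25/2.33/2.40. The fitted model was a Poisson random-intercept model with model-based standard errors. The marginal estimate is the ratio of raw proportions. Risk ratios are geometric means.

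| Latent correlation (trials) | Poisson mixed model | Marginal | Model SE / empirical SD |
|---|---|---|---|
| 0.3 (150) | 2.40/2.36/2.47 | 2.39/2.35/2.47 | 1.14/0.97/0.91 |
| 0.7 (600) | 2.55/2.58/2.65 | 2.36/2.39/2.45 | 1.15/1.10/1.05 |
| 0.9 (400) | 2.87/2.97/3.06 | 2.28/2.36/2.43 | 1.23/1.16/1.19 |

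Inflation at 12 months: 2.65/2.45 = 1.08 and 3.06/2.43 = 1.26. With no effect at correlation 0.7 (600 trials), the Poisson model gave 0.99/0.99/1.01 and rejected in 2-4% of trials.

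At rates of 5-12%, a latent correlation of 0.3 means that only 14-24% of abstainers are abstinent again at the next visit; 0.7-0.9 means 39-70%.

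**4. Effect on the risk ratio, binomial fit with capped probabilities.** The median 12-month log risk ratio was 1.13 at latent correlation 0.7 and 1.68 at 0.9, against about 0.9 marginally. As risk ratios these are exp(1.13) = 3.10 and exp(1.68) = 5.37, against exp(0.9) = 2.46. Once probabilities are capped, the coefficient is no longer the ratio of the two groups' abstinence rates.

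**The case against.** The strongest reply is that the article does not state the faulty model. It never mentions Poisson or normal random effects, and its neighbouring text points to a binomial family. Family, estimation and convergence rules are commonly left to an analysis plan. This stands in part: a missing family is no finding, and the Poisson figures are conditional. But the link and the random-effects model class are stated, and neither usual way of fitting that pair is sound here. The binomial reading fares worse than the Poisson one in the simulation.

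A second reply is that under a log link, a random intercept independent of treatment leaves the person-level and population risk ratios equal, which is a good reason to match the primary model's scale. That is true apart from the bound at 1. The bound is what matters when within-person correlation is strong.

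A reader might also infer that the plan produces wrong risk ratios in general, or error bars that are too narrow and hence false positives. Neither is supported. The Poisson bias is negligible at latent correlation 0.3 and absent with no effect. At the higher correlations the standard errors are too wide, and the null rejection rate was below 5%. Nor does anything here reach the primary test, which is a separate regression at 12 months.

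**Conclusion.** The point holds as a minor improvement to a supportive analysis. A log-link mixed model is a poor choice for correlated binary abstinence. With normal random effects, about 8-20% of the modelled abstinence lies in probabilities above 1 at the protocol's 12-month rates. The risk ratio is overstated by about 8-26% in a Poisson fit, and by more in a capped binomial fit, but only with a real effect and strong within-person correlation.

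The size rests on assumptions that the document does not supply: normal random effects, persistence of 40-80%, latent correlations of 0.7-0.9, and the 3- and 6-month rates. The capped binomial figures also depend on the cap. The primary log-binomial test and the sample size stand.

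**What to change.** For the repeated 3-, 6- and 12-month analysis only, replace the log-link mixed model with one of these:

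- **Marginal log-link model:** GEE with Poisson working variance and robust standard errors, containing intervention, time and their interaction. Run it on the data with non-completers coded as smoking, and on the multiply imputed data already planned under Missing data and dropouts.
- **Logit mixed model:** same fixed effects, reporting standardized (marginal) risk ratios by visit.

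Either keeps the risk-ratio scale of the primary analysis. In the simulation the marginal estimate at 12 months was 2.43-2.45 at latent correlations 0.7-0.9, against a true 2.40. The cost is a short change of analysis text; standard software suffices, and design and sample size are untouched. The downside of GEE is that it gives population-average effects only.
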